### Study rationale

Based on the systematic review by Kim et al. only one study has assessed the impact of financial incentive coupled with MI on treatment adherence of young adults [14]. The study was conducted using a single-site, non-randomised and applied pre- and post-test design which is not deemed to have high internal validity. Some of the established threats to the internal validity of quasi-experimental design such as pre- and post-test design include history threat, maturation threat, testing threat, lack of blinding, instrumentation, regression to the mean, selection bias and drop out [15].

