### Participants

Eligibility criteria for participants will include the following: all patients with HIV who had transitioned from pediatric stage to a young person/adult; 10–19 years irrespective of CD4+ cell count; initiated into HIV care and antiretroviral therapy for minimum of 6 months; currently off ART despite multiple attempts to restart; poor medication adherence (< 95% adherence rate assessed through pill count or self-report); willing to restart therapy and sign a written informed consent (see Additional file 2).

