### Intervention

A structured adherence support scheme termed the ‘Incentive Scheme’ will be applied to the intervention hospitals while the control hospitals will receive usual care. The Incentive Scheme added to the usual care involves financial incentives linked to viral load (VL) combined with attendance for motivational interviewing (MI) with an adherence counsellor trained in MI techniques. (Table 2) [14]. Training on MI will be in accordance with an MI guide that covers key points for MI as well as examples and key insights to assessing patient risk, risk reduction counselling and inspiring behaviour change [16]. Participants in hospitals randomised to usual care will receive the normal care obtainable in the HIV treatment hospitals. This typically involves monthly or bi-monthly scheduled hospital visit for medical examination, prescription refill and adherence counselling, bi-yearly VL assessment, and yearly CD4^+^ count analysis.

In addition to the usual care, participants in the intervention hospitals will receive MI at baseline and following initiation of ART, they will receive a gift voucher of US$5.6 when VL < 20 copies/mL at 12 weeks, a gift voucher of US$2.8 if the VL remains suppressed for the next 3 months, and the next 6 months, and finally a gift voucher of US$5.6 if the VL remains < 50 copies/mL at 1 year. All incentives will be conditional not only on patients meeting their VL target but attending for MI. Those with VL higher than the thresholds will not receive the incentive. The potential maximum cumulative financial incentive is US$16.8 if viral suppression is sustained for 12 months. The patient will have the liberty to withdraw from the scheme at any time point. Routine hospital data will be collected and outcomes will be assessed by changes in HIV VL and CD4+ count from baseline, at 12 months from enrolment and at 24 months to establish whether any benefit is seen from the intervention could be sustained when financial incentives cease. Each patient in the study will be assigned to a study nurse working in the HIV treatment hospital and they will be tracked with their mobile phone numbers.

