### Statistical analysis

Statistical analysis will be conducted using IBM SPSS for Windows, Version 20 (IBM Corp, Armonk, NY, USA). As shown in Table 3, descriptive statistics will be used to evaluate differences in demographic and clinical characteristics. Categorical variables will be expressed as frequencies or percentages and quantitative variables as means and standard deviations or medians and interquartile ranges. An intention-to-treat analysis will be conducted. A secondary per-protocol analysis will also be conducted. The latter will include only those participants who completed the treatment protocol originally allocated, providing results on the efficacy of the trial. If there is a significant difference between the intention-to-treat analysis and the per-protocol analysis, then the former will be reported. Comparison of dichotomous measurements between the intervention group and the control group will be conducted using the chi-square test (or Fisher’s exact test) while comparison of the mean of continuous measurements between the intervention group and the control group will be conducted using an independent *t* test. A two-sided *p* value of 0.05 will be used to indicate statistical significance.

**Table 3 Tab3:** Data analysis outline

Study objective	Outcome variable	Type of analysis
Objective 1: effectiveness of intervention	Primary outcome	
	HIV viral load	*χ*^2^ test or Fisher’s exact test
	Secondary outcomes	
	CD4+ count	Within group: paired-sample *t* tests or Wilcoxon signed-rank tests; between group – Student’s *t* test or Wilcoxon signed-rank tests
	Adherence to antiretroviral therapy (ART)	*χ*^2^ test or Fisher’s exact test
	Adherence to hospital appointment	Within group: paired-sample *t* tests or Wilcoxon signed-rank tests; between group – Student’s *t* test or Wilcoxon signed-rank tests
Objective 2: cost-effectiveness analysis	Cost-effectiveness of intervention	Incremental cost-effectiveness ratio
Objective 3: qualitative assessment of implementer’s perspective	Programme implementer’s perspective	In-depth interview (thematic content analysis)

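### For two secondary outcomes, CD4+ count and appointment adherence, Table 3 lists within-arm before/after tests as evidence of effectiveness, although CD4+ count should rise in both arms once ART is restarted

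*Protocol article*

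**What the plan says.** Table 3 (Statistical analysis) sets out the tests by objective. Under "Objective 1: effectiveness of intervention", the rows for CD4+ count and for adherence to hospital appointment both read "Within group: paired-sample *t* tests or Wilcoxon signed-rank tests; between group", followed by the between-group tests. The rows for HIV viral load (the primary outcome) and for adherence to ART list only a chi-square or Fisher's exact test.

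The text above the table describes comparisons between intervention and control only, and sets a two-sided 0.05 level for significance without excepting any test. Neither the text nor the table says that the within-group tests are descriptive, or that the between-group result decides.

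The Intervention section says that "outcomes will be assessed by changes in HIV VL and CD4+ count from baseline, at 12 months from enrolment and at 24 months", the later time point being there to show whether benefit lasts once incentives stop.

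The Participants section requires patients to be "currently off ART despite multiple attempts to restart", to have "poor medication adherence (< 95% adherence rate assessed through pill count or self-report", and to be "willing to restart therapy and sign a written informed consent". The criteria apply to both arms.

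The Study rationale criticises the one earlier study of incentives with motivational interviewing because it "applied pre- and post-test design which is not deemed to have high internal validity". Among the threats it lists for such designs are "history threat, maturation threat, testing threat, lack of blinding, instrumentation, regression to the mean, selection bias and drop out".

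**The concern.** Everyone enrolled is off therapy, poorly adherent and about to restart. Controls also receive prescription refills and adherence counselling as usual care. CD4+ count is therefore expected to rise from baseline in both arms even if the scheme does nothing. A paired test within one arm measures the sum of restarting treatment, regression to the mean and any scheme effect, and cannot separate them.

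Table 3 nevertheless places that test under the effectiveness objective, with the same standing as the between-group test. This allows two misleading statements. One is that the intervention arm improved significantly, offered as evidence that the scheme works. The other is that the intervention arm improved significantly and the control arm did not, offered as a difference between arms. Neither is a comparison of randomised groups. The Study rationale itself names the reasons why before/after change is weak evidence.

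**Working it through.** **The plan's sample size.** This supplies the number per arm and is not affected by the point.
- Before clustering: a difference of 12% with SD 24% is 0.5 SD. n = 2 × (1.960 + 0.842)² / 0.5² = 62.8, so 63 per group, as stated.
- With six hospitals per arm and ICC 0.047: m = 63 × (1 − 0.047) / (6 − 63 × 0.047) = 60.04 / 3.04 = 19.8, so 20 per hospital and 120 per arm, as stated.
- With three more per hospital: 6 × 23 = 138 per arm, as stated.

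**Inputs for the check.**
- From the protocol: 120 per arm and two-sided α = 0.05.
- Assumed, because the protocol gives no figure: SD of the CD4+ change 150 cells; the same true gain in both arms (no scheme effect) of 15, 25 or 50 cells; patients independent (clustering ignored).

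**Formula.** For the paired t test in one arm, the noncentrality is δ = (gain / 150) × √120 on 119 degrees of freedom, with critical value 1.980. Let p be the probability that one arm shows a significant rise. The arms are independent, so both are significant with probability p², and the intervention arm alone with probability p(1 − p).

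| Common gain | Gain / SD | δ | p | Both arms, p² | Intervention only, p(1 − p) |
|---|---|---|---|---|---|
| 15 cells | 0.10 | 1.10 | 0.191 | 0.037 | 0.155 |
| 25 cells | 0.17 | 1.83 | 0.441 | 0.194 | 0.246 |
| 50 cells | 0.33 | 3.65 | 0.952 | 0.906 | 0.046 |

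The value of p(1 − p) cannot exceed 0.25, so the 25-cell row is close to the worst case. At 138 per arm, a gain of 25 cells still gives 0.25.

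**By size of common gain.** In SD units, with 120 per arm and independent patients, the intervention arm alone is significant in 24% of trials at 0.2 SD, 9% at 0.3 SD and under 1% at 0.4 SD. The intervention arm is significant, with or without the control arm, in 58%, 90% and 99%. So a small common gain favours the one-arm-only pattern. A large one makes a significant rise in the intervention arm nearly certain, with the same in controls.

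**What a between-arm test does.** A valid two-sided 5% test would favour the intervention in 2.5% of trials with no effect, whatever the common gain. Simulation with six hospitals of 20 per arm and ICC 0.047 for the change (20,000 runs; the ICC is the protocol's assumption for viral suppression, borrowed here for CD4+ change) gave:
- t test on hospital means: two-sided error rate 5.0% to 5.3%;
- t test that ignores hospitals: 15% to 16%.

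The 2.5% benchmark is therefore met only if the between-arm test accounts for hospitals.

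**The case against.** The strongest reply is that no rule in the protocol bases a conclusion on the within-arm tests. Each affected row also has a between-group test, the text of the section speaks only of comparisons between arms, and the primary outcome is defined as a difference between groups. Harm would need an author to overlook the between-arm result reported beside the within-arm one. This stands as a limit on the point. It does not remove it, because the tests are listed under effectiveness, share the 0.05 level and carry no label.

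Stronger readings that a reader might infer are not supported:
- **That the trial's main conclusion is at risk.** Viral suppression, ART adherence, the sample size and the cost-effectiveness endpoint involve no within-group test.
- **That a false effect in one arm arises in a quarter of trials.** That figure needs a gain of about 0.17 SD. If restarting ART raises CD4+ count substantially, both arms are usually significant and the one-arm pattern is uncommon (4.6% at 50 cells).
- **That baseline attendance is low by selection.** The eligibility criteria select on being off ART and on medication adherence, not on keeping appointments. A low attendance baseline is plausible but not stated, so the quantified case rests on CD4+ count.
- **That the trial becomes the design its rationale rejects.** The rationale criticises a single-site, non-randomised study. This trial keeps a randomised control arm and between-arm tests on the same outcomes. What carries over is the weakness of before/after change as evidence.

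**Conclusion.** The point holds for two secondary outcomes, CD4+ count and adherence to hospital appointment, and for no others. Within-arm tests placed under the effectiveness objective cannot show an intervention effect in patients who all enter off ART and willing to restart, and the protocol does not label them descriptive.

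The size depends on assumptions that the documents do not supply: SD of change 150 cells, equal true gain in both arms and clustering ignored. With those and 120 per arm, a common gain of 50 cells makes both arms significant in about 91% of trials. A gain of 15 to 25 cells makes the intervention arm alone significant in about 15% to 25%. These two harms occur at different sizes of gain and should not be added together. For appointment adherence the same logic applies to any within-arm p value, but the documents give no basis for a figure.

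**What to change.** In Table 3, delete the within-group paired tests from the CD4+ count and hospital appointment rows under Objective 1. Report within-arm change at 12 and 24 months descriptively, as means with intervals and no p values. Add a sentence to the Statistical analysis section stating that effectiveness on these two outcomes rests only on the between-arm comparison, and that this comparison accounts for clustering by hospital. The clustering clause is needed because, under the protocol's own ICC, the planned independent t test would not hold its 5% level.

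Removing the within-group tests is one table edit. It needs no extra data or patients and does not change the sample size. Accounting for hospitals changes the between-arm method but needs no new data beyond each participant's hospital.

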## Methods/design

### Study objectives

The main aim of the present study is to use the rigour of a randomised controlled trial (RCT) to evaluate the impact of financial incentive and MI on adolescents’ linkage, retention and adherence to antiretroviral therapy and HIV care in Anambra State, Nigeria. A cost-effectiveness analysis alongside the cluster randomised trial will be conducted as a secondary aim to assess the cost per additional patient achieving viral suppression through the proposed intervention. In-depth interview (IDI) with all the healthcare providers in the intervention arm will be conducted at the end of the study to assess their perspective on the programme’s feasibility. The main outcome will be measured at the level of an individual adolescent. Cluster randomisation is being chosen for practical reasons and to prevent treatment group contamination.

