### Trial design

The study will be a cluster randomised controlled trial. Clusters are HIV treatment hospitals in Anambra state. Hospitals (the clusters) will be matched by type of hospital (e.g. secondary or tertiary) and the paired units will be randomly assigned to the intervention or the control arm. The trial has two periods – intervention period and post-intervention period. Each of these periods will run for a 1-year duration. Further details of the trial are shown in Tables 1 and 2 and Additional file 1. Figure 1 shows the schedule of enrolment, interventions and assessments for the trial design.

**Table 1 Tab1:** The World Health Organisation (WHO) trial registration dataset

Data category	Information
Primary registry and trial identifying number	The Pan African Clinical Trials Registry: https://pactr.samrc.ac.za/ (PACTR201806003040425)
Date of registration in primary registry	2 February 2018
Source of monetary or material support	European Developing Countries Clinical Trial Partnership (EDCTP)
Primary sponsor	Nnamdi Azikiwe University
Contact for public queries	[contact]
Public title	Conditional Economic Incentive and Motivational Interviewing to Improve Adolescents’ Retention and Adherence to Antiretroviral Therapy and Care in South East Nigeria: a Cluster Randomised Trial
Scientific title	Conditional Economic Incentive and Motivational Interviewing to Improve Adolescents’ Retention and Adherence to Antiretroviral Therapy and HIV Care in South East Nigeria: a Cluster Randomised Trial
Country of recruitment	Nigeria
Health condition or problem studies	HIV
Interventions	Conditional economic incentive and motivation interviewing
Key inclusion criteria	All patients with HIV who had transitioned from pediatric stage to a young person/adult; age 10–19 years irrespective of CD4+ cell count; currently off antiretroviral therapy (ART) despite multiple attempts to restart; willing to restart therapy and sign a patient agreement
Study type	Interventional
Date of first enrolment	Yet to commence
Target sample size	240
Recruitment status	Yet to commence
Primary outcome	HIV viral load
Key secondary outcome	CD4+ count, adherence to ART (measured using pill count) and adherence to appointment with hospital

**Table 2 Tab2:** Protocol for conditional economic incentives

Started ART	VL response and attended for MI	Voucher value (USD)
Week 12	VL < 20	5.6
6 months suppressed	Sustained VL < 20	2.8
9 months suppressed	Sustained VL < 20	2.8

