### Outcomes

The primary outcome for the trial will be the difference between groups in the proportion with HIV VL suppression (≤ 20 copies/mL) by 12 months and 24 months. The secondary outcome measure will include the average change in CD4+ count, adherence to ART (measured using pill count) and adherence to an appointment with the hospital for individual participants. Viral load analysis will be done using the COBAS TaqMan 96 and the Amplilink software.

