### Sample size

The sample size was calculated using a web-based sample size calculator of the UCSF Clinical and Translational Science Institute [17]. The sample size calculation is based on the proportion of patients with VL suppression ≤ 20 copies/mL – the main outcome measure. Based on a power of 80% and an α of 0.05 (two-sided), 63 patients per group will be needed to observe a 12% (assumed standard deviation of 24%) increase in the number of participants with VL suppression as previously reported [18]. After adjustment for the cluster design, based on the assumed intracluster correlation coefficient of 0.047 and a fixed cluster per arm of six HIV treatment hospitals, the effective sample size increased to 120 patients per arm (i.e. a total of 240 participants). Due to potential attrition that could arise as a result of severe adverse events, treatment failures or the participant simply deciding to withdraw, we added three participants per hospital increasing the number of participants in each arm to 138 (i.e. a total of 276 participants). A fixed number of six clusters or hospitals per arm (i.e. 12 hospitals in total for the trial) were informed by the fact that only 12 hospitals in Anambra State offer comprehensive HIV services including HIV-adherence counselling and antiretroviral treatment services and these 12 hospitals have appreciable HIV client load. Each of the hospitals will, therefore recruit 23 participants.

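### Table 3 names a paired test (Wilcoxon signed-rank) for comparing two unpaired arms on CD4+ count and appointment adherence

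*Protocol article*

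**What the plan says.** Table 3 (Statistical analysis) has a row for CD4+ count and a row for adherence to hospital appointment. Each names a within-group and a between-group method. Within group, it is the paired t test with the signed-rank test as alternative. Between group, it is Student's t "test or Wilcoxon signed-rank tests", so the same rank test serves both purposes.

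The text above the table treats the arms as independent: "comparison of the mean of continuous measurements between the intervention group and the control group will be conducted using an independent" t test. It names no rank-based alternative.

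On CD4+, Outcomes states: "The secondary outcome measure will include the average change in CD4+ count". Intervention adds: "outcomes will be assessed by changes in HIV VL and CD4+ count from baseline, at 12 months from enrolment and at 24 months". Baseline CD4+ therefore enters the outcome by subtraction. No baseline-adjusted model is named.

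On the unit of measurement, Study objectives says: "The main outcome will be measured at the level of an individual adolescent". The only matching described is of hospitals, which are "matched by type of hospital (e.g. secondary or tertiary) and the paired units will be randomly assigned" to the arms.

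**The concern.** The signed-rank test is a one-sample test on within-pair differences. It is the right rank partner for the paired t test and the wrong one for Student's two-sample t test. Used between arms at participant level, it needs each adolescent in an intervention hospital to be tied to one in a control hospital, and nothing in the design creates such pairs.

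If the data lead the analyst to the rank-based option, the plan as written either cannot be carried out or gives an answer that depends on how the file happens to be sorted. A pairing chosen after seeing the data could move the result across 0.05. Because the entry appears in both rows, it governs two of the three secondary outcomes.

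**Working it through.** **The plan's own figures.** The protocol states no figure for CD4+ or appointment adherence. Its sample size is for viral suppression: "Based on a power of 80% and an α of 0.05 (two-sided), 63 patients per group will be needed". That reproduces. For a difference of 12% and SD of 24%, n = 2 × (1.96 + 0.842)² × (0.24/0.12)² = 62.8, so 63 per group. With 6 hospitals per arm and an intracluster correlation of 0.047, the number per hospital is 63 × (1 − 0.047) / (6 − 63 × 0.047) = 60.04 / 3.04 = 19.76, rounded to 20, which gives 120 per arm. I take 120 per arm as the working size below.

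**Can the test be computed?** It needs equal numbers and a one-to-one link. The protocol adds three participants per hospital for attrition (20 + 3 = 23; 6 × 23 = 138 per arm), so it expects losses, and equal final numbers would be a coincidence. With 120 in one arm and 118 in the other, the paired computation fails.

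**What if the arms happen to be equal?** Two independent normal samples of 120 per arm were simulated 4,000 times without clustering, with rows paired arbitrarily:

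| | Signed-rank | Rank-sum |
|---|---|---|
| Type I error at nominal 5% | 5.0% | 5.2% |
| Power at a difference of 0.36 SD | 75.9% | 76.6% |

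On average, then, arbitrary pairing does little harm. Within a single dataset it matters. One simulated dataset was re-paired at random 2,000 times. The signed-rank p ran from 0.0004 to 0.10, with the middle 95% between 0.003 and 0.035 and a median of 0.012. The rank-sum test does not depend on row order and gave p = 0.017.

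**Could hospital pairs be meant?** Twelve hospitals make at most 6 pairs. The smallest two-sided signed-rank p is then 2/2⁶ = 2/64 = 0.031. The next attainable value is 4/64 = 0.0625, so significance at 0.05 would need all six differences in the same direction.

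**Rank-sum on hospital summaries.** For 6 against 6 there are 12!/(6! × 6!) = 924 arrangements, so the smallest two-sided p is 2/924 = 0.002. This counts unrestricted allocations.

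**Change score against baseline adjustment (CD4+ only).** Let r be the correlation between baseline and follow-up CD4+, with equal variances at both times. The variance of the change score is proportional to 2(1 − r), and the residual variance after adjusting for baseline is proportional to 1 − r². The ratio is (1 − r²) / [2(1 − r)] = (1 + r)/2. The document gives no r, so a range is assumed:

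| r (assumed) | Ratio | Reduction |
|---|---|---|
| 0.5 | 0.75 | 25% |
| 0.7 | 0.85 | 15% |
| 0.9 | 0.95 | 5% |

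This is participant-level arithmetic and leaves clustering aside.

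**The case against.** The strongest defence is that this is a slip of the pen for rank-sum. The text above the table already specifies an independent t test, and only a fallback for two secondary outcomes is affected. That is plausible and it limits the weight of the point, but the table is where the plan names its tests and it names the wrong one twice.

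A second defence is that hospitals are matched, so a signed-rank test on six hospital differences would be legitimate. It would be, but no such analysis is described. The test is offered as the alternative to Student's t, the text calls the comparison independent, and the Randomisation section describes allocation within strata of clinic type rather than within pairs.

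A reader might infer four stronger points that the document does not support:

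- *Baseline CD4+ is not used.* It is used, because the outcome is defined as change from baseline. Comparing change between randomised arms is valid, so covariate adjustment is a gain in efficiency and not the repair of an error. Equal variances are also an assumption that may not hold, since participants enter off ART and then restart.
- *The signed-rank p value is meaningless or inflates false positives.* The simulation shows type I error near 5%. The accurate complaint is dependence on row order, and failure with unequal arms.
- *Appointment adherence has no baseline to pair with.* This is not established. Participants must have been in care and on ART for at least 6 months, usual care has scheduled visits, and routine hospital data are collected. Earlier attendance may be available; the article does not say which pair of measurements is meant.
- *The within-group tests are meant as the treatment effect.* Table 3 lists them under effectiveness, but beside the between-group tests, and nowhere says so. Since participants in both arms restart therapy, CD4+ may rise in both, so it is worth stating that these tests do not carry the conclusion.

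**Conclusion.** The point holds, at modest weight. Table 3 states a paired test for an unpaired comparison in two secondary-outcome rows, and this conflicts with the independent-samples approach in the text of the same section. Participant-level signed-rank cannot be run with unequal arms. With equal arms it gives a p value that varies with row order, from 0.0004 to 0.10 in the example. That range comes from one simulated, unclustered normal dataset; it illustrates the mechanism and does not forecast this trial's data.

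Baseline adjustment for CD4+ stands only as an improvement available at no data cost. Its size, 25% to 5% lower residual variance, rests on an assumed correlation of 0.5 to 0.9 and on equal variances. The primary outcome and the sample size are untouched.

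**What to change.** - In both Table 3 rows, replace the between-group signed-rank test with the Wilcoxon rank-sum (Mann-Whitney) test, applied to the 12 hospital summaries (6 against 6). Swapping the name alone and testing individual participants would leave hospital clustering ignored. If the final allocation is restricted by pairs or strata, the reference distribution should follow it, and the smallest attainable p will then be larger than 0.002.
- For CD4+, state in the table that change from baseline is the quantity compared. Preferably, compare CD4+ at 12 and 24 months between arms with baseline CD4+ as a covariate and a random hospital effect.
- State that the treatment effect rests on the between-arm comparison and that within-arm changes are reported descriptively. For appointment adherence, say which two measurements any within-person comparison uses.
- Bring the sentence on continuous outcomes in the Statistical analysis text into line with the table.

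The cost is a few words in Table 3 and in that sentence, plus one model specification if the CD4+ improvement is adopted. Baseline CD4+ is already part of the outcome, so no new data are needed.
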